**Project info**

**Project title**

|               |                                                                                                                                           |
|---------------|-------------------------------------------------------------------------------------------------------------------------------------------|
| Project title | Longitudinal Study of music Therapy's Effectiveness for Premature infants and their caregivers: international randomized trial (LongSTEP) |
|---------------|-------------------------------------------------------------------------------------------------------------------------------------------|

**Primary and secondary objectives of the project**

|                                  |                    |
|----------------------------------|--------------------|
| Primary and secondary objectives | Primary objective: |
|----------------------------------|--------------------|

**Longitudinal Study of music Therapy's Effectiveness for Premature infants and their caregivers: international randomized trial (LongSTEP) (Forskerprosjekt - BEHANDLING)**

Application Number: ES592623 Project Number: -1

1. To provide high-quality evidence of the effects of music therapy on bonding between preterm infants and their parents during neonatal hospitalization and in primary care post-discharge.

Secondary objectives:

2. To examine effects of music therapy on premature infants' general and socio-emotional development and social behaviour.
3. To examine effects of music therapy on premature parents' depression and stress.
4. To examine medical and social factors of premature infants and their parents that may be associated with music therapy, including use of services.
5. To prepare for examining cost-effectiveness and longer-term evaluation of effects beyond the first year of life.

## Project summary

Background: Preterm birth is a major medical, psychological and socio-economic problem worldwide. Music therapy (MT) is part of best practice in neonatal care in some countries, but is only emerging in Norway. A recent systematic review suggests positive effects of MT for preterm infants and parents/caregivers, but methodologically rigorous studies including long-term follow-up of infant and parental outcomes are missing.

Objectives: Our aim is to provide evidence of the impact of MT on infant/caregiver bond, caregiver well-being and infant development. We will examine the effectiveness and feasibility of implementing MT within the Norwegian, European and international context, bridging specialist care and municipal health care settings. We will also provide the basis for examining cost-effectiveness and long-term outcomes beyond the project period.

### Project summary

Methods: The study is a 2x2 factorial, international multi-center, assessor-blind pragmatic randomized controlled trial evaluating the longitudinal effect of MT on preterm infants and primary caregivers across 12 months. MT will be delivered during NICU and/or during a post-discharge 6-month period. The Postpartum Bonding Questionnaire will be used to evaluate bond. Parental depression will be assessed with Edinburgh Postnatal Depression Scale, and parental stress with Parental Stress Scale. Other standardized scales will be used to assess infant psycho- and socio-emotional development.

Discussion: This study fills a gap in knowledge by assessing the longer-term impact of MT for preterm infants/caregivers, and of MT beyond the hospital context. Study outcomes are directly applicable to the development of clinical practice and will inform future research, theory and practice on a national and international level. By incorporating family-centered care, continuity of care,

**Longitudinal Study of music Therapy's Effectiveness for Premature infants and their caregivers: international randomized trial (LongSTEP) (Forskerprosjekt - BEHANDLING)**

Application Number: ES592623 Project Number: -1

user involvement, and cultural relevance, this study contributes to improved rehabilitation.

## Funding scheme

### Supplementary info from applicant

|                                                                                                             |                                                                                                           |
|-------------------------------------------------------------------------------------------------------------|-----------------------------------------------------------------------------------------------------------|
| Programme / activity                                                                                        | BEHANDLING                                                                                                |
| Application type                                                                                            | Forskerprosjekt                                                                                           |
| Topics                                                                                                      |                                                                                                           |
| Other relevant programmes/ activities/projects                                                              |                                                                                                           |
| Discipline(s)                                                                                               | Psychology, music therapy, pediatrics                                                                     |
| If applying for additional funding, specify project number                                                  |                                                                                                           |
| Have any related applications been submitted to the Research Council and/or any other public funding scheme | Yes                                                                                                       |
| If yes, please provide further information                                                                  | We submitted a similar project last year, which was rejected then, but it has been revised substantially. |

## Progress plan

### Project period

|           |          |
|-----------|----------|
| From date | 20180101 |
| To date   | 20211231 |

# **LONGITUDINAL STUDY OF MUSIC THERAPY'S EFFECTIVENESS FOR PREMATURE INFANTS AND THEIR CAREGIVERS: INTERNATIONAL RANDOMIZED TRIAL (LONGSTEP)**

## **1. RELEVANCE**

The proposed project is an **international multicenter pragmatic randomized controlled trial (RCT)** assessing the longitudinal impact of music therapy's (MT's) effects on a **clinically relevant primary endpoint** in premature infants and their parents. Preterm birth is "one of the **largest single conditions in the Global Burden of Disease analysis**" [1], with high mortality and risk of lifelong impairment. This trial will determine whether MT as delivered by a qualified music therapist during neonatal intensive care unit (NICU) hospitalization and/or in community care after discharge to home is superior to standard care in improving **bonding between** primary caregivers and preterm infants, an outcome that is linked to **parental well-being and infant development**. Building on promising results from **phase II studies and meta-analyses**, LongSTEP is the **first phase III trial** worldwide of MT's effectiveness for premature infants and their caregivers. This project promotes **continuity of care** by **bridging specialist and municipal health care** contexts, and uses **family-centered developmental care** to treat the infant within the family context. This protocol links **two health regions** in Norway with international clinical sites in **five countries** (Norway, Sweden, Germany, Israel, and Columbia). **Outcomes** are **clinically relevant** and use **electronic health registry data** where this is possible. It features **interdisciplinary collaboration** between neonatologists, psychologists, music therapists, trial methodologists, biostatisticians, and health economists; preparations towards a full **cost-effectiveness** analysis are included. **User representatives** have confirmed the project's importance and relevance and will continue to be **involved in all aspects** from planning and conducting the trial to disseminating and implementing its findings. LongSTEP has strong potential for publication in high-ranked international journals and will contribute to future practice development, theory, and research. Findings will be **directly applicable to clinical practice**, and will have a valuable impact for infants from an at-risk group, their primary caregivers, and the practitioners working with them. MT is relevant for both **genders** and can be tailored to **minorities** with different cultural backgrounds.

## **2. ASPECTS RELATING TO THE RESEARCH PROJECT**

### **2.1 BACKGROUND AND STATUS OF KNOWLEDGE**

The global average preterm birth rate is around 11% worldwide corresponding to 15 million preterm infants each year [1, 2]. Over one million die as a direct result of prematurity and another million show lifetime impairment [3]. With advancements in medical technology, a growing number of neonates as young as 23 to 24 weeks gestational age (GA) with birth weight as low as 500 grams are surviving in high-income countries. In Norway, 3275 children (5.5%) were born at 28-36 weeks GA, and 230 (0.5%) at 22-27 weeks GA in 2012 [4]. Preterm infants have higher risks of mortality, morbidity, and various postnatal complications. With improved survival rates, there is growing concern for long lasting complications including behavioral and mental health problems, and poorer quality of life [1]. Moreover, the economic burden of preterm birth includes increased cost of neonatal care, long-term costs associated with complex health status, and lost economic productivity over life [5].

Prematurity strongly impacts caregivers. Premature labor is perceived as a stressful [6], traumatic [7, 8], unexpected event that interrupts mothers' antenatal bonding and preparation for delivery. Families can experience higher levels of stress, anxiety, and fear for the infant's safety, as well as insecurity and powerlessness [8, 9]. Mothers are at risk for postpartum depression, posttraumatic stress disorder, feelings of guilt, mourning, and lack of self-worth. Separation due to NICU stay and prolonged hospitalization can complicate the development of healthy infant/parent bonding and adversely impact the formation of secure attachment [8, 10]. Preterm birth and subsequent hospitalization can impair the mother-infant relationship, which plays a central role in the child's socio-emotional development and formation of future intimate relationships [11, 12]. Mothers' psychological well-being [13] or postpartum depression [14] are the most important factors affecting infant/parent relationship in the postnatal period. Decreasing maternal stress and

reducing early separation during NICU hospitalization are crucial aims for positively impacting long-term outcomes [15].

MT is part of NICU standard treatment in some hospitals in several countries. MT in infant critical care involves the informed use of music and a therapeutic relationship to promote infant development and facilitate secure attachment with primary caregivers [16]. MT promotes infant sensory regulation and encourages neurological development [17, 18]. Incorporating parents as active partners in implementing NICU-MT decreases infant and parent distress [19], which may promote bonding. MT beneficially impacts infant physiological parameters, behavior state, weight gain and feeding ability, and may reduce hospital stay [17, 20-24]. In a rigorous, updated systematic review and meta-analysis of RCTs we confirmed a large, favorable effect of MT on respiratory rate and maternal anxiety [25]; however, several areas require further investigation. Rigorously designed and adequately powered studies using standardized outcome measures and interventions implemented by music therapists with specialized NICU training are required. Parallel RCTs to evaluate long-term effects of MT, and extending intervention periods past discharge from NICU are required to assess long-term impact, a substantial gap in present knowledge [25]. Studies examining longitudinal provision of MT tailored to different stages of infant development [19] and long-term effects of MT on the development of healthy infant/parent bonding and secure attachment are needed [17, 25].

**Objectives: see grant application form.**

## **2.2 APPROACHES, HYPOTHESES AND CHOICE OF METHOD**

### **2.2.1 Study design**

We propose a factorial (2x2), multi-center, assessor-blind pragmatic RCT to evaluate the longitudinal effect of MT in NICU and/or after discharge on premature infants and their primary caregivers across a 12-month time period (Fig. 1). The factorial design will allow testing the independent effect of each combination: NICU-MT, post-discharge MT, both, or neither, as well as interactions between them. Participants will initially be recruited from the NICU of participating hospitals according to the following in- and exclusion criteria:

- (1) Infants: Born below 35 weeks GA, of both genders, any ethnicity, from single or multiple pregnancies, who have achieved sufficient medical stability (as determined by medical staff) to start MT.
- (2) Primary caregivers: One of the parents/caregivers must provide written, informed consent before any study procedures occur. Primary caregivers should agree to engage in at least 2 of the 3 MT sessions per week during NICU, and/or in 5 of the 7 MT post-discharge sessions. To ensure feasibility, primary caregivers should live within reasonable commuting distance from the treating NICU in order to be eligible for participation.

The 2x2 factorial design entails a two-phase protocol covering both the stay in the NICU and municipal care after discharge from hospital. During NICU stay, participants will be randomly allocated to receive either MT integrated in standard NICU care or standard NICU care alone. Before discharge to home, participants will again be randomly allocated to either MT integrated in municipal care or standard municipal care. Standard care may include other early intervention methods of care with the exception of other music-based approaches. Treatment fidelity (adherence and competence) will be evaluated by independent raters using video recordings.

### **2.2.2 Interventions**

The MT approach in this study is informed by models previously described and tested [18, 21, 25, 26]. Like other MT models [26], it is based on the notion that infants have a capacity to communicate actively [27, 28]. As in some newer models, parents are actively involved and empowered [21, 29]. The approach here thus builds on an emerging consensus, but is more explicit in its adaption to developmental levels and emphasis on infant/parent co-regulation. Furthermore, unlike previous studies [25], MT is extended beyond the tertiary care setting to help with the transition to daily life and municipal care. MT focuses on supporting positive relationship formation within the infant/parent dyad by promoting beneficial co-regulation, and includes psychosocial support of the parent.

**MT during NICU:** Participants will be offered individual MT sessions 3 times/week for 20-30 minutes/session, with a maximum of 36 sessions per infant (assuming a maximum NICU stay of 9 weeks). NICU-MT will be provided for all eligible infants once they achieve medical stability, usually after 26 weeks postmenstrual age (PMA; defined as GA at birth plus the time since birth [30]). A flexible protocol of procedures matched to infant PMA, familial/cultural preferences, and infant's demonstrated readiness to receive stimulation, will occur as individually-tailored sessions at bedside:

*Approximately 26 to 31.99 weeks PMA – Cautious use of sung/toned voice:* The music therapist shows caregivers how to use facilitated tucking and midline alignment (if appropriate for the infant) along with

[figure not shown]

**Figure 1. Flow-chart illustrating the design**

*Note.* ADBB –Alarm Distress Baby Scale; ASQ:SE – Ages and Stages Questionnaire: Social-Emotional; BSID – Bayley Scales of Infant and Toddler Development; CA – corrected age; EPDS – Edinburgh Postnatal Depression Scale; Med/Soc – medical and social factors as detailed in text; PBQ – Postpartum Bonding Questionnaire; PSS – Parental Stress Scale.

sung or toned voice to pacify the infant, promote state regulation, and enable bonding, by using simple melodies or modifying songs of kin [21] into a lullaby style matched to infant responses. Use of sung/toned voice is adjusted in response to infant engagement/disengagement cues. The infant may be resting in his/her isolette with the portal door open, resting swaddled in his/her basinet or bed, or swaddled and cradled in a static manner by the caregiver (consistent with Kangaroo care) or the therapist. MT may occur during Kangaroo care, if Kangaroo care is part of standard care.

*32 to 35.99 weeks PMA – Cautious use of multimodal stimulation:* This phase applies as soon as the infant demonstrates readiness to receive additional sensory stimulation. The therapist reviews infant engagement/disengagement cues with the caregiver, describes techniques used in multimodal stimulation [18], models the progressive sequence, and supports caregivers in implementing it themselves: (1) Swaddling

and cradling infant statically (without tactile or vestibular stimulation at first). (2) Commencing contingent singing/humming of simple melodies or modified songs of kin while cradling infant. (3) Adding gentle massage while singing and cradling infant (delivered in cephalocaudal and proximodistal order [18]). (4) Gently rocking while providing massage, singing/humming, and cradling. (5) If the infant has begun opening his/her eyes, using vocal inflection to promote eye opening, eye contact, and responses to social cues (e.g., smiling, cooing). The sequence will be paced and modified according to infant engagement/disengagement cues, and will be reversed or paused in response to disengagement cues.

**From 36 weeks PMA – Engagement in musical exchange:** This phase applies when the infant demonstrates readiness to engage in more interactive levels of musical exchange. Caregivers interact musically with the infant, using vocal inflection and sung cues to encourage the infant to achieve a quiet, alert state and engage in eye contact, vocalization, and rudimentary social interaction. Depending upon infant readiness, caregivers may use premature infant-friendly, basic musical toys to promote auditory localization, auditory tracking, visual tracking, eye contact, reaching, grasping, and mouthing. The therapist will encourage the caregiver to use preferred lullabies and children’s songs or to modify songs of kin [21] in order to encourage musical dialogue with the infant.

**Standard care during NICU:** This will vary across countries, but will typically include necessary medical care and a limited amount of interventions to reduce stress among infants and to inform and promote safety in parents [31].

**MT post-discharge from hospital:** Individual MT sessions will be offered, minimum 5 and maximum 7, 45-minute sessions per infant/parent distributed across six months. These will occur at municipal child health centers or at home, and comprise: (1) Verbal greeting and brief discussion of infant’s progress (approx. 5 min). (2) Musical greeting of infant and caregiver, encouraging caregiver to participate (5 min). (3) Engagement in musical exchange following the procedures described in the “from 36 weeks” category above, with therapist modelling musical engagement (approx. 10 min). (4) Discussion of current infant/parent challenges and strategies for using musical interactions to address these needs, with therapist modelling musical techniques to promote self-regulation or to facilitate musical interaction, depending upon needs identified by the caregiver (approx. 10 min). (5) Caregiver demonstration of techniques discussed during session (approx. 10 min). (6) Musical closure and reminder of planned timing for next visit (approx. 5 min). Any siblings may be involved if desired by the caregiver. Subsequent sessions will follow a similar sequence, adjusted to infant developmental level and ongoing needs. The therapist will work in close dialogue with those providing standard aftercare procedures.

**Standard care post-discharge from hospital:** This includes follow-up visits and preventive interventions in primary or specialist health care as needed. Preventive interventions during the first year of life are focused on growth/eating/nourishment as well as psychomotor/sensory development and also include a focus on families and bonding [31]. According to our user representative (see separate document), support on psychological issues may however be limited and sometimes insufficient or inadequate.

### 2.2.3 Outcomes

Outcomes will be assessed at several time points: at baseline; one to two days before discharge to home; at 6 months corrected age (end of MT; primary endpoint); and 12 months of corrected age (CA; chronological age reduced by number of weeks born preterm [30]). Data collectors and assessors will be trained in assessment procedures and blinded to participant allocation; success of blinding will be verified.

**Primary outcome: Bond between primary caregiver and infant** will be evaluated at all time points (**primary time point: 6 months CA**) using the Postpartum Bonding Questionnaire (PBQ). PBQ is a self-rating screening instrument for disorders of the early mother-infant relationship consisting of 25 statements on a six-point Likert scale (each 0-5; sum score ranging from 0 to 125; high = problematic), addressing problems in the mother-infant relationship based on weakened bonding; rejection and anger; anxiety about care; and risk of abuse [32]. The scale is validated and widely used in clinical practice and research [33]. It has been translated and tested in several languages and cultures [34] and has high internal consistency [35] and test-retest reliability [32], also in the Norwegian version [36].

#### **Secondary outcomes:**

(1) **Infant development** will be assessed blindly using the Bayley Scales of Infant and Toddler Development (BSID). It covers cognitive, language, and motor development and is considered the gold standard for assessing development of young and premature infants up to 42 months [37].

(2) **Re-hospitalization** during the first year of life (excluding outpatient visits), based on electronic health records: Safely bonded parents panic less when an infant develops fever and may be more capable of

handling minor illnesses of their infants. A previous study [29] found a promising difference of 15% with music therapy compared to 30% with standard care.

(3) Infant *socio-emotional development* will be evaluated using the Ages and Stages Questionnaire Social-Emotional (ASQ:SE). This is a parent-completed questionnaire that targets social-emotional competence and problem behaviours, with 19 to 22 Likert-scaled items depending on child age [38, 39].

(4) Infant *social behaviour* will be assessed using the Alarm Distress Baby Scale (ADBB) [40]. It covers facial expression, eye contact, general level of activity, self-stimulating gestures, vocalizations, response to stimulation, relationship. It has shown high sensitivity, specificity and reliability [40].

(5) *Parental depression* will be assessed with the Edinburgh Postnatal Depression Scale (EPDS). The 10-item self-report instrument assesses caregiver's postpartum depressive symptoms, focusing specifically on more severe problems rather than those that are common to nearly all new mothers (such as loss of energy, feeling tired, changes in appetite and sexual drive). It has shown high sensitivity and specificity in two Norwegian studies [41, 42].

(6) Level of parental stress will be assessed with the Parental Stress Scale (PSS). This is a self-report 18-item questionnaire that assesses *stress levels associated with parenting* [43].

(7) In addition, a checklist of *medical and social factors* will be completed at baseline and updated 1-2 days prior to discharge, to track the presence of particular factors that might impact infant responsiveness (e.g., intraventricular hemorrhage, presence and nature of sedation, abnormal hearing screening at discharge, etc.), or parental engagement (e.g., socioeconomic status, receiving treatment for mental health or substance use problems, etc.). Within the MT group, physiological signs (heart rate, respiratory rate and oxygen saturation) and behavior state will be informally monitored during the course of MT as part of the provision of infant-directed approaches. This part will also assess use and costs of medical services. Existing electronic health records will be used wherever possible to improve reliability and completeness and to reduce costs and burdens of data collection.

**Cost-effectiveness:** We will collect the data that are necessary for analyzing cost-effectiveness both from a health services perspective (i.e. costs of all treatments incurred within the health sector) and from the broader societal perspective (i.e. including also indirect costs such as productivity losses). If clinical effectiveness is found, we will apply for separate funding to analyze incremental cost-effectiveness ratios and willingness to pay. Otherwise, these data will be used to describe the context in which the treatment took place.

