where  $PBQ_{it}$  denotes the PBQ score for participant  $i$  at measurement  $t$ ,  $time_t$  the time from baseline at measurement  $t$  and  $gr_i$  the randomization group of participant  $i$ .  $\beta_0$ ,  $\beta_1$ ,  $\beta_2$  and  $\beta_{12}$  are the coefficients estimated in the model,  $U_i$  is an individual random term per participant and  $\varepsilon_{it}$  an independent, identically distributed error term. In the second step we refine the model to take into account both randomization steps, leading to the extended model:

$$PBQ_{it} = \beta_0 + \beta_1 time_t + \beta_2 grR1_i + \beta_{12} time_t grR1_i + \beta_3 grR2_i + \beta_{13} time_t grR2_i + U + \varepsilon_{it} ,$$

with the same notation as above and  $grR1_i$  and  $grR2_i$  denoting the groups from the first and second randomization, respectively. In these models  $\beta_1$  describes a group-independent time effect,  $\beta_2$  and  $\beta_3$  a time-independent group effect, and  $\beta_{12}$  and  $\beta_{13}$  the time-dependent change of the group effect. We will investigate both linear and simple contrasts (comparing each time point with the baseline) in time to assess the treatment effect. The same analyses will be done for the secondary outcomes; using an analogous generalized linear mixed model for binary outcomes. Per-protocol analyses will include those who received at least 6 MT sessions in the NICU and at least 5 MT sessions post-discharge, respectively; these are considered the minimum numbers for the intervention to be successful. Additionally, we will conduct exploratory statistical analyses for prespecified subgroups (sex; GA at birth [ $<28$  wks, 28 to  $<32$  wks, 32 to  $<35$  wks]; hearing status at discharge [normal vs. abnormal]; bonding at baseline [PBQ impaired bonding score  $\geq 11$  vs.  $<11$ ]) as well as qualitative/mixed-methods analyses of process data to maximize learning.

**Data management plan:** To promote transparency and applicability of trial results and to facilitate re-analysis by other researchers while also protecting anonymity, de-identified individual patient data will be made available through the Norwegian Centre for Research Data (NSD).

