**4.4 ETHICAL PERSPECTIVES:** Ethical approval will be secured before start of recruitment from the Regional Committee for Medical Research Ethics in Western Norway (REK Vest), as well as data security clearance from NSD, and corresponding bodies in the other participating countries. The study will be registered in the ISRCTN database before the first patient's first visit. Informed consent will be obtained postnatally following routine practices in the NICU. Trial staff will inform parents/caregivers about consent for participation. The parent/caregiver will receive written and oral explanation of the proposed research project including aims, duration of involvement, expected benefits to participants and others, nature of the interventions, procedures involved in participation, and any potential risks. It will be emphasized that enrolment in the study is voluntary, that parent/caregivers can withdraw at any time from all or part of the study, and that any decision they take in this respect will have no bearing on the care the infant and family receive. Participants will be informed that the outcomes of the study will be published, but that no details will be divulged from which the participant could be identified. The primary caregivers will also be informed who to contact in an emergency and how to discontinue participation if desired. The consent form will be available in Norwegian and English, and other participating countries will create translations as needed. All significant harms as well as unintended effects for each group will be collected and described. Special forms to report trial-related adverse events will be developed, and all professionals involved in the trial will be informed about how to identify and report adverse events. Any serious adverse effects that occur will be reported, and if related to MT, will be reported to the DMC.

**4.5 GENDER ISSUES (RECRUITMENT OF WOMEN, GENDER BALANCE AND GENDER PERSPECTIVES):** Both boys and girls born prematurely will be included. Primary caregivers of both genders will be included in this trial, although we anticipate that predominantly mothers will be participating in MT sessions. The gender distribution of researchers in the core team and among collaborators is balanced. The role of PI will be handed to a female researcher after the first year (see above).

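### Harms are promised for each group, but no collection method common to all arms is specified, while MT families meet trial staff far more often; unequal detection is a risk

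*Combined protocol and SAP*

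**What the plan says.** The commitment on harms is in section 4.4 (Ethical perspectives): "All significant harms as well as unintended effects for each group will be collected and described". The same paragraph gives the means. On the instrument: "Special forms to report trial-related adverse events will be developed". On who is to report, it states that "all professionals involved in the trial will be informed about how to identify and report adverse events". Escalation depends on attribution: "Any serious adverse effects that occur will be reported, and if related to MT, will be reported to the DMC".

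No section gives a definition of an adverse event, a schedule for asking about events, or a requirement that the source be the same in every arm.

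Contact with trial staff is set elsewhere. Section 2.2.2 offers NICU-MT three times a week, and post-discharge MT as "minimum 5 and maximum 7, 45-minute sessions per infant/parent distributed across six months". Section 2.2.3 gives every family four assessments: baseline, just before discharge, 6 months corrected age and 12 months corrected age. Secondary outcome (7) in the same section adds: "Within the MT group, physiological signs (heart rate, respiratory rate and oxygen saturation) and behavior state will be informally monitored during the course of MT". The sentence goes on to present this monitoring as a component of giving MT.

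Three sources do work identically in all arms: the assessments by blinded data collectors, the medical and social checklist (baseline, updated before discharge), and re-hospitalization from electronic records. None is named as a route for adverse events.

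**The concern.** A by-group account of harms is informative only if the same event has the same chance of being recorded in each group. Here the named reporters are people in the trial, and one group sees such people several times a week in the NICU and repeatedly after discharge. The other has no scheduled trial contact between the assessments.

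Attribution adds a second asymmetry. An event in an infant receiving only standard care can hardly be classed as trial-related, and cannot be related to MT, so neither the form nor the route to the monitoring committee is built to capture it.

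At stake is whether the harms table can be read across its columns. An excess under MT could reflect closer watching, and a low standard-care rate could reflect events that nobody wrote down. Events that leave no trace in records cannot be recovered at analysis.

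**Working it through.** The plan states no harms figure to reproduce. The check is a count of planned contacts, followed by an illustration.

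**1. Planned contacts with trial staff**

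Inputs: the maximum of 36 NICU sessions and the 5 to 7 post-discharge sessions (section 2.2.2); the per-protocol minima of 6 NICU and 5 post-discharge sessions (section 2.2.4), used as the lower bound; four assessments for everyone (section 2.2.3).

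| Group | MT sessions | With 4 assessments |
|---|---|---|
| MT in both phases | 6 + 5 = 11 to 36 + 7 = 43 | 15 to 47 |
| NICU-MT only | 6 to 36 | 10 to 40 |
| Post-discharge MT only | 5 to 7 | 9 to 11 |
| No MT | 0 | 4 |

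The NICU maximum conflicts with its own stated basis: 3 sessions a week for 9 weeks is 27, not 36. The two figures must be reconciled. With 27, the top of the first row is 27 + 7 = 34 sessions, or 38 contacts. The pattern does not change.

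The two phases should be read separately. The second randomization is 1:1 among those remaining, so post-discharge sessions should be balanced across the NICU arms. The NICU contrast is exposed to the NICU sessions, and the post-discharge contrast to the 5 to 7 later ones.

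**2. What unequal detection could do**

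Observed risk = true risk × probability of being noticed. With the same true risk in both arms, the apparent risk ratio is simply the ratio of the detection probabilities. The true risk (10%) and all detection probabilities below are assumptions; the documents give none.

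| Noticed, MT | Noticed, standard care | Observed risks | Apparent risk ratio |
|---|---|---|---|
| 90% | 90% | 9% vs 9% | 1.0 |
| 90% | 70% | 9% vs 7% | 1.29 |
| 90% | 50% | 9% vs 5% | 1.8 |
| 90% | 30% | 9% vs 3% | 3.0 |
| 70% | 90% | 7% vs 9% | 0.78 |

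The last row covers the opposite case, in which therapists under-report events from their own sessions.

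With 250 / 2 = 125 infants per NICU arm, one can also ask how often a nominal two-sided 5% test would be significant. Using Φ((|p1 − p2| − 1.96 × SE0) / SE1), with SE0 pooled and SE1 unpooled, the middle three rows give about 8%, 24% and 52%. The plan contains no such test, so these figures only indicate how visible the distortion could be in a table.

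**The case against.** Four stronger readings are tempting, and the documents do not support them.

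- *Infants are observed only in the MT group.* They are not. All arms have NICU and follow-up care, blinded assessors, the checklist and record-based re-hospitalization. Only the in-session monitoring is confined to MT, and it is described as part of delivering MT. No section says it feeds the harms data.
- *Intraventricular hemorrhage and hearing results are never compared by arm.* The checklist is secondary outcome (7), and section 2.2.4 extends the primary analyses to the secondary outcomes. The hearing result is also a subgroup variable ("hearing status at discharge [normal vs. abnormal"). What is missing is their designation as safety outcomes.
- *The harms comparison is biased and would show an excess with MT.* The documents establish a risk. Size and direction are unknown.
- *A false finding of harm can be given a probability.* A true rate of 20%, with 90% noticed under MT and 45% under standard care, gives 18% vs 9% and about 55%. The arithmetic is right, but the rates are assumed and the plan only describes harms.

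The other side has two further arguments. The professionals involved in the trial are not defined and could include medical staff or primary-care contacts who see both arms. The forms were openly deferred, an independent monitoring committee is planned, and the amendment tables refer to a published protocol that is not among the documents reviewed. Both are fair, and both keep this a question of risk. Neither supplies a common form, schedule or source, and neither removes the attribution filters. A table by group invites comparison even when nothing is tested.

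**Conclusion.** The concern holds as a specification gap that carries a risk of bias. The plan promises harms by group but names only reporting by trial professionals on forms limited to trial-related events, with escalation restricted to effects related to MT. Planned trial contact runs from 4 for a family with no MT to between 15 and 47 for a family with MT in both phases.

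The contact count rests on the documents' session figures, with the per-protocol minima as the lower bound. The risk ratios rest wholly on assumed detection probabilities and must not be read as estimates for this trial. Re-hospitalization, read from records, does not depend on therapist contact and is largely outside the problem.

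The change should be made. It is cheap, and it has to be settled at data collection.

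**What to change.** Revise section 4.4 as follows.

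(a) Ask every caregiver in all four groups the same fixed harms questions at the existing discharge, 6-month and 12-month assessments. Record every event whatever its judged relation to MT or to the trial.

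(b) Base the by-group harms table on those answers, plus events read the same way in all arms from records and the checklist: deaths, re-hospitalization, and new intraventricular hemorrhage and abnormal hearing screening at the discharge update. Label these as safety outcomes. Compare the last two by first-randomization arm, since they belong to the NICU phase.

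(c) Report what therapists observe during sessions separately, as a description of MT sessions with no control column.

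The cost is a few minutes at each existing visit and one extra table, with no added visits or staff. A limit remains: caregivers know their allocation, so their answers may still differ by arm. The opportunity to report would be equal, and the record-based items do not depend on caregiver report.
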